### Study design

2.1

The BENCHMARK registry will document the effect of introducing tailored BENCHMARK QoC measures (Table 1) into TAVI centers using four distinct phases: Retrospective baseline evaluation phase, education phase, implementation phase, and prospective effect documentation phase (Figure 1). For the baseline evaluation phase (retrospective phase), each center will retrospectively document 30 consecutive patients (*N* = 900) undergoing transfemoral TAVI with a balloon expandable transcatheter aortic valve before introducing the BENCHMARK QoC measures. The TAVI procedure and patient discharge within this phase must have been performed prior to the first educational phone call. For each patient, follow‐up data after 1 and 12 months will be recorded. In the education phase, each center will identify a defined leadership team (i.e., multidisciplinary heart team) to undergo online education on the BENCHMARK QoC measures and best practices. A detailed description of the education phase is shown in Figure 2. During the Implementation Phase, consisting of a 2‐month time window, each center will introduce the tailored QoC measures into their hospital routine. Follow‐up calls will be arranged between the BENCHMARK education team and each center every 2 weeks to offer assistance with regard to implementation progress. Finally, each center will prospectively enroll 50 consecutive patients (*N* = 1500) undergoing TAVI after completing the education and implementation phases. This prospective phase is estimated to be 20 months duration overall, with up to 8 months for patient recruitment and 12 months follow‐up for the last patient included.

**TABLE 1 clc23711-tbl-0001:** BENCHMARK QoC measures

BENCHMARK QoC measures	Implementation description
1. Education of patient and family	The patient, and if the patient is not independent, at least one family member or carer is involved in the patient‐education, and discharge provision is discussed with them prior to the procedure.
2. Education and alignment of the internal team (medical and paramedical)	At least one joint meeting per year is organized to educate all staff involved in the diagnostics, post‐procedural care and intervention of patients with severe AS.

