**FIGURE 2 clc23711-fig-0002:**
[figure not shown]
Education pathway (BENCHMARK QoC measures). Pathway stages 1–4: (1) center self‐assessment is performed prior to the online education seminar; (2) online center education on BENCHMARK QoC measures will be arranged by the education team (including the local steering committee member and/or the PI team and the registry management team). A minimum of 3 TAVI Team members, having been identified as a leadership team (TAVI coordinator and further staff members per site), will attend the seminar; (3) a post‐QoC education call to discuss the self‐assessment results and write a final action plan with the leadership team will be arranged 1 week after the education seminar; and (4) a follow‐up call will be arranged to review center progress on BENCHMARK QoC implementation. PI, principal investigator; QoC, quality of care

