### Data collection

2.4

Clinical outcome data collected will be based on the center's standard of care for TAVI. Data will be collected according to the timetable set out in Table 3, and include physical assessments, medical history and symptoms, diagnostics, electrocardiography (ECG), echocardiography (Echo), hospitalization and procedural duration, safety parameters, QoL measures, satisfaction surveys, as well as resource utilization parameters. Data will be captured in an eCRF by either a study nurse or physician, and the registry sponsor will check all data for plausibility and completeness.

**TABLE 3 clc23711-tbl-0003:** Data collection schedule

	Baseline evaluation phase (retrospective documentation phase)					Effect documentation of BENCHMARK QoC measures (prospective enrollment phase)				
	Screening/baseline	TAVI	Discharge	30 days visit *Visit or call* (±1 week)	12 months visit *Visit or call* (±3 weeks)	Screening/baseline	TAVI	Discharge	30 days visit (±1 week)	12 months visit (±3 weeks)
Signed informed consent	X^a^					X^b^				
Inclusion/exclusion criteria	X					X				
Referral management	X					X				
Treatment decision	X					X				
Tasks, being impacted by the coordinator								X		
Demographics	X					X				
ECG and Echo	X	X	X	X^c^	X^c^	X	X	X	X	X
Comorbidities	X					X				
Symptoms and social characteristics	X					X				
Risk score (Euro Score II)	X					X				
Frailty, mental, social status	X					X				
Quality of life (TASQ)						X		X	X	X
Procedural details (device success)		X					X			
Length of hospital stay			X					X		
Safety and efficacy variables (VARC‐2)^27^			X	X	X			X	X	X
Rehospitalization data				X	X				X	X
Adverse event reporting		X	X	X	X		X	X	X	X
BENCHMARK QoC measures (center and patient based)								X		
Patient/physician/coordinator/nursing staff satisfaction			X^d^					X		
Self‐reported working hours per patient (physician, coordinator, nursing staff)								X		

Abbreviations: ECG, electrocardiogram; Echo, echocardiogram; IRB, institutional review board; TAVI, transcatheter aortic valve implantation; QoC, quality of care; TASQ, Toronto Aortic Stenosis Quality of Life Questionnaire; VARC‐2, Valve Academic Research Consortium‐2 consensus document.

^a^
The TAVI and discharge visits of patients being eligible for retrospective documentation must have been documented prior to site's education on BENCHMARK QoC measures. Need for consent form according to local IRB requirements.

^b^
Consent needs to be given prior to the TAVI procedure.

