^c^
30 day and 12 months follow‐up (retrospective phase) either hospital visit (preferred) or performed via phone call (no ECG/Echo will be available for this option).

^d^
Optional: Survey could be administered to retrospective patients in combination with consent form (e.g., via postal way).

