Reduce the use of human resources, patient flow optimization	To reduce staff workload and to perform timely delegation of responsibilities to minimize the physiciansˈ workload: Working hours per patient collected from physicians, nursing staff, medical technical assistant, TAVI coordinator Economic assessment of working hours needed To increase number of patients with severe AS undergoing TAVI per day to reach higher hospital efficiency: Mean number of interventions performed per day/per week (on center level)
Maintenance of patient safety	To ascertain uncompromised safety post TAVI, by successful TAVI performance and reduced procedural complications: Device success and procedural complications: Device success Conduction disturbance Pacemaker implantations Conversion to open heart surgery Moderate or severe paravalvular leak Safety at 30 days and 12 months (VARC‐2)^27^: Mortality (cardiac/non‐cardiac) Stroke/TIA Major vascular complications PPM (at 30 days) (Cardiac) hospital readmission Number and type of adverse events: Economic assessment with regard to avoided TAVI associated complications
Improvement of patient QoL as well as patient and staff satisfaction	To improve patient QoL and satisfaction, to achieve relief of staff workload, and to make sure that improved structures are translated into patient relevant outcomes: Patient QoL assessment (TASQ) Patient satisfaction (tailored survey) Physician/Coordinator satisfaction (tailored survey)
Improved QoC by implementation of BENCHMARK QoC measures	To increase the implementation progress of the BENCHMARK QoC measures per center over time to document the structural achievement in the patient pathway (center self‐assessment on a monthly basis, patient based assessment in the eCRF): Rating of 8 BENCHMARK QoC measures (rating 0%–100%)

Abbreviations: AS, aortic stenosis; CCU, Coronary Care Unit; eCRF, electronic case report form; TAVI, transcatheter aortic valve implantation; ICU, intensive care unit; IMC, immediate care; OR, operating room; PPM, permanent pacemaker implantation; Pts, patients; QoC, quality of care; QoL, quality of life; TASQ, Toronto Aortic Stenosis Quality of Life Questionnaire; VARC‐2, Valve Academic Research Consortium‐2 consensus document.

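### The baseline patient satisfaction survey is optional and tied to the consent form, and no staff survey before education is described, so the satisfaction objective lacks a like-for-like comparison as documented

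*Protocol article*

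**What the plan says.** Table 4 (section 2.5) lists as a secondary objective "Improvement of patient QoL as well as patient and staff satisfaction". Its instruments are the TASQ for quality of life and tailored surveys for satisfaction; the staff item reads "Physician/Coordinator satisfaction (tailored survey".

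Table 3 (section 2.4) has a single row, "Patient/physician/coordinator/nursing staff satisfaction", marked under Discharge in both phases. The prospective mark is unqualified. The retrospective mark carries footnote d: "Optional: Survey could be administered to retrospective patients in combination with consent form (e.g., via postal way".

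Three other statements fix the setting:

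- Section 2.1, on the retrospective phase: "The TAVI procedure and patient discharge within this phase must have been performed prior to the first educational phone call".
- Table 3 footnote a, on retrospective consent: "Need for consent form according to local IRB requirements". Table 2 likewise lets the local committee agree to inclusion without a signed form.
- Table 3 footnote b, on prospective consent: "Consent needs to be given prior to the TAVI procedure".

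Section 2.2 bases the sample size on being able to detect changes in outcomes between the two phases. Figure 2, stage 1, describes a contact with staff before education: "center self‐assessment is performed prior to the online education seminar".

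**The concern.** Read without its footnote, Table 3 offers a matched measurement: the same survey, at discharge, before and after the QoC measures. The footnote shows that the two marks do not describe the same measurement. One is scheduled for every patient at discharge. The other is a centre option, travels with a form that some centres may not need, and reaches people whose admission is already over.

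The registry would then hold two sets of patient scores under one row heading, in a design built to compare phases. A difference between them could come from the QoC measures, from the interval since discharge, from the setting in which the form was filled in, or from who answered. Later analysis cannot recover answers that were never collected or realign the interval, so this is a matter of design and not one to leave to an analysis plan.

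For staff the difficulty is different. The row names physicians, coordinators and nurses and carries a baseline mark, but the only procedure attached to that mark concerns patients.

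**Working it through.** **1. The planned numbers.** 30 centres × 30 = 900 retrospective patients, 30 × 50 = 1500 prospective patients, total 2400. This reproduces the article's figures. No response rate, effect size or variability is given for satisfaction, so the figures in steps 3 to 5 rest on assumptions.

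**2. The two patient measurements side by side.**

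| | Retrospective | Prospective |
|---|---|---|
| Status | optional | unqualified mark |
| Carrier | consent form, itself dependent on the local committee | discharge visit |
| Time | Discharge column, but discharge is already past (inferred) | discharge |
| Mode | not fixed; post is an example | not stated |
| Who can answer | patients reachable and willing, at centres using the option | enrolled patients at discharge |

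Status and carrier are stated. Completion after discharge is an inference, but a strong one: a patient enters this cohort only if treatment and discharge came before the first education call, and the survey goes out with the consent form for the retrospective documentation. The length of the interval is not given.

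**3. How many baseline answers?** Responses = 900 × share of centres opting in × reply rate.

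- Half opt in, 40% reply: 900 × 0.5 × 0.40 = 180 (20%).
- Half opt in, 70% reply: 900 × 0.5 × 0.70 = 315 (35%).
- All opt in, 40-70% reply: 360 to 630 (40-70%).

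**4. What selective reply could do.** Assume true satisfaction p = 80% in both phases, so no real change, and complete prospective response (n = 1500). Let k be the reply probability of satisfied baseline patients relative to dissatisfied ones.

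Observed baseline = pk / (pk + 1 − p).

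- k = 0.67: 0.536 / 0.736 = 72.8%, a spurious gain of 7.2 points.
- k = 0.8: 0.64 / 0.84 = 76.2%, a spurious gain of 3.8 points.
- k = 1.25: 1.00 / 1.20 = 83.3%, a spurious loss of 3.3 points.
- k = 1.5: 1.20 / 1.40 = 85.7%, a spurious loss of 5.7 points.

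Probability that a two-sided 5% comparison of proportions calls this artefact significant, with 270 to 630 baseline replies (30-70% of 900), by normal approximation Φ[(|Δ| − 1.96·SE₀)/SE₁], with SE₀ pooled and SE₁ unpooled:

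| k | 270 replies | 630 replies |
|---|---|---|
| 0.67 | 0.74 | 0.95 |
| 0.8 | 0.30 | 0.50 |
| 1.25 | 0.24 | 0.43 |
| 1.5 | 0.60 | 0.89 |

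Example for k = 0.67 and 270 replies: Δ = 0.0717, SE₀ = 0.0270, SE₁ = 0.0290, so Φ(0.65) = 0.74. The direction of k is unknown, so the artefact could flatter or hide an effect.

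**5. Bounds without a reply model.** If 80% of responders are satisfied and a share r replies, the true baseline lies between 0.8r and 0.8r + (1 − r): 24-94% at r = 0.3, 40-90% at r = 0.5, 56-86% at r = 0.7.

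**6. Staff.** The Table 3 row names three staff groups and has the baseline mark. Footnote d, the only text attached to that mark, speaks of retrospective patients. No other part of the article describes a staff satisfaction survey before education. Table 4 lists physicians and coordinators, and Table 3 adds nursing staff. Row, footnote and objective do not match.

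**The case against.** The best case against this point is that it reads possibilities as rules. Footnote d is permissive, and post is only an example, so a reader might infer that every baseline survey is postal and completed months later, but the text does not say so. That stands. The conclusion needs only that the survey is optional and comes after discharge.

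A reader might also infer that staff have no baseline at all. The documents do not support that. The mark sits on a row naming staff, the footnote may have been meant only for patients, who need a special route once they have left, and the full protocol may describe a staff survey. What can be said is that the article describes none.

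Third, no test of satisfaction is specified. Section 2.6 gives generic methods that may be used, and Table 4 states an aim. It would be wrong to say that the article commits itself to a before-after test of satisfaction. But the objective is worded as improvement, in a design that compares phases, and the optional survey is the only baseline for patients that it shows.

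Fourth, section 3.2 admits potential confounding and bias with limited scope for adjustment, and no retrospective cohort can be surveyed at a discharge already past. Both are true. The limitations do not, however, name a difference in how or when satisfaction is measured, and a limit inherent in the design is a reason to restrict the conclusion.

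Finally, the response rates and bias figures are assumed. They show what could happen and are not evidence that it will.

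**Conclusion.** The point holds in a limited form. As documented, baseline and prospective patient satisfaction differ in timing and selection, and possibly in mode, so a difference between phases cannot be attributed to the QoC measures. For staff, the Table 3 row and footnote d do not match, and no survey before education is described.

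The size cannot be fixed from the documents. Under the assumptions shown, baseline response could be 20-35% or 40-70% depending on how many centres opt in, and moderate selective reply could produce an apparent change of about 3 to 7 points in either direction where none exists. These figures rest on an assumed 80% true satisfaction, complete prospective response and the chosen reply ratios.

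This concerns part of one secondary objective. Length of stay, ICU use and safety are unaffected. It is a cheap improvement to what the registry can conclude.

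**What to change.** **Patients.** Report satisfaction at discharge descriptively for the prospective phase, and do not use the optional baseline survey to support a claim of improvement. If that survey is kept, report its response rate by centre, label the comparison exploratory, and compare it only with a prospective survey given by the same mode at a similar interval after discharge.

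**Staff.** Reconcile the Table 3 row with footnote d, and align the staff groups in Tables 3 and 4. At centres not yet educated, give the existing staff survey with the self-assessment that already precedes the seminar (Figure 2, stage 1) and repeat it at the end of prospective enrolment. At centres already educated, report staff scores descriptively only. The Abstract gives a start in April 2021, so this may apply to many of them.

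**Cost.** A weaker satisfaction claim, one extra staff survey per centre at a contact that already takes place, and some rewording. The repeat at the end of enrolment follows a different schedule from the discharge mark in Table 3, so the table should show it. Keeping a patient comparison would add a post-discharge mailing or call in the prospective phase; dropping it avoids that.

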### Registry objectives

2.5

The primary objective of the BENCHMARK registry is to document the effect of introducing tailored BENCHMARK QoC measures into TAVI centers to (1) decrease length of hospital stay; and (2) reduce the need for ICU capacity. Secondary objectives will be to streamline diagnostics, minimize staff workload allowing timely delegation of responsibilities, ascertain uncompromised patient safety post‐TAVI (VARC‐2 defined early and time‐related valve safety), improve patient quality of life (QoL), patient and staff satisfaction, and improve the implementation of BENCHMARK QoC measures by each center over time. A full description of the primary and secondary objectives of the BENCHMARK registry is provided in Table 4.

**TABLE 4 clc23711-tbl-0004:** BENCHMARK registry objectives

Primary objectives	
Reduction in length of hospital stay	To reduce the length of hospital stay (door to needle, needle to door, overall stay) in order to reduce overall costs based on hospitalization, and to enable early return to normal life: Separate single hospitalization for diagnostics Door to needle (days) Needle to door (days) Timely discharge to home, rehabilitation center or other institution Economic effect assessment associated with hospitalization changes after implementation of BENCHMARK QoC measures
Reduction of the need for ICU capacity	To accelerate the post‐procedural patient care recovery pathway: Minimize/eliminate time spent in the recovery room, ICU, CCU or IMC and prioritize a rapid return to general ward, in order to reduce the level of invasiveness of post procedural care (e.g., with regard to COVID‐19): Time spent in the recovery room (hours) Time spent on the ICU (hours) Time spent on the CCU (CCU) (hours) Time spent on the IMC (hours/days) Time spent on the general ward (hours/days)

Secondary objectives	
Streamlining of diagnostic and procedural times	To streamline diagnostics to avoid duplication of diagnostic measures and to tighten schedules: Proportion of repeated diagnostic procedures Patient status assessment: physician versus nurse/coordinator To reduce the procedural time without compromising patient safety post TAVI: Time between incision and sheath removal (min) Time between entering and leaving the OR/catheterization laboratory/hybrid room (min)
Reduce the use of human resources, patient flow optimization	To reduce staff workload and to perform timely delegation of responsibilities to minimize the physiciansˈ workload: Working hours per patient collected from physicians, nursing staff, medical technical assistant, TAVI coordinator Economic assessment of working hours needed To increase number of patients with severe AS undergoing TAVI per day to reach higher hospital efficiency: Mean number of interventions performed per day/per week (on center level)
Maintenance of patient safety	To ascertain uncompromised safety post TAVI, by successful TAVI performance and reduced procedural complications: Device success and procedural complications: Device success Conduction disturbance Pacemaker implantations Conversion to open heart surgery Moderate or severe paravalvular leak Safety at 30 days and 12 months (VARC‐2)^27^: Mortality (cardiac/non‐cardiac) Stroke/TIA Major vascular complications PPM (at 30 days) (Cardiac) hospital readmission Number and type of adverse events: Economic assessment with regard to avoided TAVI associated complications
Improvement of patient QoL as well as patient and staff satisfaction	To improve patient QoL and satisfaction, to achieve relief of staff workload, and to make sure that improved structures are translated into patient relevant outcomes: Patient QoL assessment (TASQ) Patient satisfaction (tailored survey) Physician/Coordinator satisfaction (tailored survey)
Improved QoC by implementation of BENCHMARK QoC measures	To increase the implementation progress of the BENCHMARK QoC measures per center over time to document the structural achievement in the patient pathway (center self‐assessment on a monthly basis, patient based assessment in the eCRF): Rating of 8 BENCHMARK QoC measures (rating 0%–100%)

Abbreviations: AS, aortic stenosis; CCU, Coronary Care Unit; eCRF, electronic case report form; TAVI, transcatheter aortic valve implantation; ICU, intensive care unit; IMC, immediate care; OR, operating room; PPM, permanent pacemaker implantation; Pts, patients; QoC, quality of care; QoL, quality of life; TASQ, Toronto Aortic Stenosis Quality of Life Questionnaire; VARC‐2, Valve Academic Research Consortium‐2 consensus document.

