### Patients

2.2

A total number of 2400 patients aged ≥18 years old with symptomatic AS who undergo TF TAVI with a balloon‐expandable transcatheter aortic valve will be included. Approximately 900 consecutive patients will be documented in the retrospective baseline evaluation phase (30 per center) and 1500 patients in the prospective phase (50 per center). The sample size estimate is based on the ability to discriminate any changes in outcomes between the retrospective baseline evaluation phase and the prospective effect documentation phase.

All patients irrespective of transcatheter valve type or access route, will be documented in an electronic case report form (eCRF) based patient logbook. A defined core data set will be collected for all patients (mortality, stroke, time of discharge/length of hospital stay, readmission).

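### Quality of life (TASQ) and working hours per patient are collected only after implementation, so the objectives to improve the one and reduce the other have no comparator

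*Protocol article*

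**What the plan says.** Section 2.5 and Table 4 list the secondary objectives. One row is "To improve patient QoL and satisfaction, to achieve relief of staff workload". It ties these aims to the improved structures reaching patients and names TASQ as the quality-of-life measure. Another row aims to reduce staff workload. Its measures are working hours per patient, an economic assessment of those hours and, at centre level, the mean number of interventions per day or week.

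Section 2.2 says that the sample size serves the detection of "changes in outcomes between the retrospective baseline evaluation phase and the prospective effect documentation phase". The planned numbers are about 900 "consecutive patients will be documented in the retrospective baseline evaluation phase (30 per center) and 1500 patients in the prospective phase (50 per center").

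Table 3 has five visit columns for the retrospective phase and the same five for the prospective phase. The row "Quality of life (TASQ") and the row for self-reported "working hours per patient (physician, coordinator, nursing staff") are marked in prospective columns only. Satisfaction has a retrospective mark with footnote d: "Optional: Survey could be administered to retrospective patients in combination with consent form". Under section 2.1, prospective patients are enrolled only after a centre has completed education and implementation.

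**The concern.** Improving quality of life and reducing workload through the care measures are effect objectives. In this design an effect can be seen only by comparing the retrospective with the prospective phase. If an outcome is never collected in the retrospective phase, that comparison does not exist. This is not a detail that an article may leave to an analysis plan, because a plan cannot analyse data that the schedule does not collect.

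Two conclusions are at stake. The only TASQ contrast left is before versus after TAVI within the prospective cohort, and a gain there is to be expected whether or not the care measures do anything. For working hours there is a single post-implementation value per patient, so the linked economic assessment has no pre-programme figure from which to calculate a saving.

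**Working it through.** **1. The plan's own numbers.** Section 2.2 gives 30 and 50 patients per centre at 30 centres: 30 × 30 = 900, 30 × 50 = 1500, and 900 + 1500 = 2400. This reproduces the stated total.

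**2. Schedule by column.** Number the Table 3 columns 1–5 (retrospective: screening, TAVI, discharge, 30 days, 12 months) and 6–10 (prospective, same order).

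| Row | Retrospective | Prospective |
|---|---|---|
| Length of hospital stay | 3 | 8 |
| Safety and efficacy (VARC-2) | 3, 4, 5 | 8, 9, 10 |
| Rehospitalization | 4, 5 | 9, 10 |
| TASQ | none | 6, 8, 9, 10 |
| Working hours per patient | none | 8 |
| Satisfaction | 3 (optional) | 8 |
| QoC measures | none | 8 |

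The first three rows fall in matching positions in both halves, so the blanks for TASQ and working hours do not look like a table that was misread.

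**3. What can be identified.** Let V be the mean TASQ change due to the valve procedure and B the extra change due to the care measures.

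- Prospective change from before to after TAVI = V + B.
- The same change in the retrospective phase would be V, but it is not collected.
- B is the difference between the two (plus any case-mix or calendar-time difference), so it cannot be separated from V.

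For working hours, let H be the mean before the programme and D the programme's effect. The prospective phase observes H + D. H is not collected, so D is not identified.

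**4. Size of the gap.** The scheduled comparator is 0 of about 900 patients for both outcomes. The variance of a between-phase difference is proportional to 1/n₀ + 1/1500, which is undefined at n₀ = 0. More prospective patients would not help.

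**5. What a partial TASQ comparator could show (illustration only).** The article gives no alpha, power or SD. Assume two-sided alpha 0.05, 80% power, no clustering by centre, and all 1500 prospective patients responding. The detectable difference in SD units is (1.960 + 0.842) × √(1/n₀ + 1/1500):

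- n₀ = 900: 2.802 × 0.04216 = 0.118 SD
- n₀ = 450: 2.802 × 0.05375 = 0.151 SD
- n₀ = 225: 2.802 × 0.07149 = 0.200 SD

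Under these assumptions even a quarter of the baseline cohort could detect about 0.2 SD. Clustering and non-response would make these figures larger. The main weakness of such a comparison would be selection, not sample size.

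**The case against.** The strongest reply is that the gap is narrow, and much of that stands. The primary objectives are length of stay and ICU capacity. Length of stay is scheduled in both phases, and section 2.3 excludes baseline patients whose stay or ICU time is incomplete. Safety and rehospitalization are also collected in both phases. Only parts of two secondary rows of Table 4 are affected.

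A reader might go further and infer any of the following. The article does not support them.

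- *That the implementation objective also fails, because "BENCHMARK QoC measures (center and patient based") is marked only at prospective discharge.* Patient-level ratings do lack a baseline. But the objective is progress per centre over time, and Figure 2 places a centre self-assessment before the education seminar while Table 4 makes it monthly. A before-and-after series exists at the level that the objective names.
- *That satisfaction has no baseline, or only a postal one.* An optional survey of retrospective patients is allowed, and post is given only as an example. It is weak because it is optional, depends on who responds, and footnote d mentions patients but not staff.
- *That the whole workload row is empty.* Interventions per day or week at centre level belong to the same row and need no patient questionnaire. They measure throughput, however, and do not replace hours per patient.
- *That the registry plans to report post-TAVI TASQ gain as a programme benefit.* Section 2.6 names no TASQ analysis. The risk lies in how the objective is worded, not in a stated plan.

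None of this supplies a comparator for TASQ or for working hours per patient, and the limitations in section 3.2 do not mention the gap.

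**Conclusion.** The point holds for two outcomes, TASQ and working hours per patient, and for the economic assessment built on those hours. As scheduled, none of the approximately 900 baseline patients contributes to either, so the effect of the care measures on them cannot be estimated. The prospective TASQ series can describe recovery after TAVI but cannot show what the measures added. A satisfaction comparison is possible but selective.

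This rests on reading Table 3 as the complete schedule for both phases. It does not rest on any assumed effect size; the detectable differences above are illustrations only. Because the primary comparison, safety and centre-level implementation are untouched, this should be fixed but does not put the registry's main conclusion at risk.

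**What to change.** 1. Reword the quality-of-life and working-hours objectives as descriptive: to describe TASQ and working hours per patient in the prospective phase.
2. State in section 3.2 that no BENCHMARK effect on TASQ, working hours or the linked working-hours economics will be inferred, and label any between-phase satisfaction comparison as exploratory.
3. Where a baseline patient's 12-month contact is still ahead and local consent arrangements allow, add TASQ to it and compare phases at 12 months with case-mix adjustment.
4. A between-phase comparison of working hours would need the same per-patient form used before education begins. A single form per centre would not be comparable with the prospective per-patient reports, because the method of measurement would differ between phases.

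Items 1 and 2 cost only wording. Item 3 adds a small burden at an existing contact and has limits that should be stated: there is no pre-TAVI value, the data come only from survivors who respond, and baseline contacts may be by phone while prospective visits take place in hospital. For patients whose 12-month contact has passed, TASQ at that time point cannot be recovered. Item 4 is possible only at centres not yet educated; elsewhere items 1 and 2 are the whole remedy for working hours.
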